#### Secondary outcome measures

A secondary outcome measure will be self-efficacy expectations of dealing with psychologically difficult situations. This will be measured quantitatively using an interval-scaled instrument newly developed for this study (pre- and post-completion of the online intervention).

Satisfaction with the intervention will be surveyed quantitatively using Likert-scales, and qualitatively using free-text responses immediately after completion of the intervention (t_1_) and semi-structured follow-up interviews. Follow-up interviews will also explore helpful strategies to reduce stigma and improve knowledge.

### Statistical analysis

For pre-post comparisons (SOSS-SF, LOSS-SF, and self-efficacy expectation scores), we will use the t-test for dependent samples (all three scales are interval-scaled). Kolmogorov-Smirnov test will be used to test normal distribution. Analyses will be conducted for participants who have completed pre and post measurement of SOSS-SF, LOSS-SF, and self-efficacy expectation (“completers”). In case of single missing values, the restricted maximum likelihood-method will be applied. Age, gender and nature of suicide experience (self-afflicted, close person like a friend or family member, interested person) will be considered for subgroup and regression analyses. Participants who have started the intervention but have not completed will be compared to completers in terms of age, gender, and nature of suicide experience, provided data is available. To access the acceptance of the intervention, dropout rate will be calculated. Satisfaction with the intervention will be evaluated descriptively (mean values and standard deviations). All analyses will be conducted using the statistics program IBM SPSS 25 [47]. For all analyses α ≤ 0.05 will be considered statistically significant.

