### Study design

The evaluation of the interactive online intervention draws on the evaluation, lessons and evidence of *The Ripple Effect* [31]. A mixed methods design with three measurement points will be realized. Prior to commencing the interactive online intervention (t_0_), sociodemographic and clinical data, attitudes and knowledge on suicidality (SOSS-SF and LOSS-SF) are collected. An interval-scaled questionnaire will also be developed—based on Bandura’s self-efficacy concept [58, 59]—to assess self-efficacy expectations when dealing with psychologically difficult situations. Psychometric properties of the new survey instrument will be described using the intervention sample. On completion of the intervention (t_1_), a post-survey will be conducted using SOSS-SF and LOSS-SF again (interval between t_0_ and t_1_ is dependent on the time participants take to complete the intervention). At a third time point (t_2_) (12–26 weeks after completion of the intervention), follow-up telephone interviews will be conducted with ten participants who agree to participate in a semi-structured telephone interview.

Due to the exploratory nature of the survey (first use of the intervention and survey tools in the German-speaking region) and the aim to allow participation from all interested persons, we decided against a randomised controlled design. The influence of the intervention on stigma and knowledge is examined, with a pre-post-design, according to the Australian example [31]. Further, qualitative information (e.g. individual experiences with the intervention) will be gathered in free-text fields as well as in follow-up interviews.

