### Sample size calculation

As for *The Ripple Effect* [31], a conservative power calculation was performed (not accounting for repeated measures). In a pre-post comparison a sample size of *N* = 241 will be necessary to identify an effect size of d = 0.20 with a power of 0.80 and a significance level of α = 0.05 (dependent t-test, alpha adjusted for two endpoints: SOSS-SF and LOSS-SF). Assuming a dropout rate of 30%, a sample of *N* = 344 is needed at the beginning of the intervention (t_0_).

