### Outcome measures

#### Primary outcome measures

Primary outcome measures will be change in suicide stigma and suicide literacy, measured quantitatively using the validated assessment tools SOSS-SF [46] and LOSS-SF [42] (pre- and post-completion of the online intervention).

Similar to *The Ripple Effect* [31], we will adapt the SOSS-SF from a general measure of suicide stigma to assess (1) negative attitudes towards oneself because of own suicidality (self-stigma), and (2) thoughts about how others think of suicidal persons (perceived-stigma).

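### The REML rule for missing values cannot be carried out in a completers-only paired t-test, a secondary scale gates the primary analysis set, and dropouts' baseline scores go unused

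*Protocol article*

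**What the plan says.** All references are to the protocol article, Aim 3, unless stated.

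- **Endpoints.** Under Primary outcome measures, the two primary outcomes are change in suicide stigma (SOSS-SF) and in suicide literacy (LOSS-SF). Self-efficacy, measured with a newly developed instrument, is listed under Secondary outcome measures.
- **Test.** Statistical analysis: "we will use the t-test for dependent samples (all three scales are interval-scaled").
- **Analysis set.** The same section: "Analyses will be conducted for participants who have completed pre and post measurement of SOSS-SF, LOSS-SF, and self-efficacy expectation".
- **Missing data.** The next sentence: "In case of single missing values, the restricted maximum likelihood-method will be applied". No mixed model is named anywhere in the article.
- **Dropout check.** "Participants who have started the intervention but have not completed will be compared to completers in terms of age, gender, and nature of suicide experience", where the data exist.
- **Timing.** Study design collects SOSS-SF and LOSS-SF before the intervention starts (t0). On completion (t1), "a post-survey will be conducted using SOSS-SF and LOSS-SF again". That sentence leaves out self-efficacy, although Secondary outcome measures says it is measured before and after.
- **Planned loss.** Sample size calculation allows for 30% dropout: 344 starters for 241 analysed.

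**The concern.** Three things in one paragraph do not fit together.

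1. The missing-data sentence names an estimation method for a model that is not planned. An analyst following the text has no step to carry out, and different analysts would fill the gap differently.
2. One joint analysis set serves all three scales, so a missing secondary scale removes a person whose primary data are complete.
3. Baseline scores are collected from people who later drop out, but the plan uses them neither in the estimate nor in the check on who drops out. These are the variables that would best show whether completers are a selected group.

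At stake is what the headline change describes. The study aims are not limited to people who finish. The Discussion makes keeping the intervention online after the study depend on its having met its aims. The article also expects change to depend on the starting level, since it anticipates a ceiling effect in users with high literacy (Strengths and limitations, E-mental health interventions).

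**Working it through.** **1. The plan's own figure.** Paired t-test from the noncentral t, d = 0.20, power 0.80, two-sided α = 0.05/2 = 0.025: n = 241 (power 0.8015). Starters: 241/0.70 = 344.3, against 344 stated. The sample size reproduces and is not in question.

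**2. Can the REML sentence be executed?** Take each possible meaning.

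- *Items missing within a scale.* REML is not an item-imputation method.
- *A mixed model fitted to completers.* This returns the paired t-test. In one simulated data set (344 starters, 236 completers) both gave a change of −0.260 and t = −3.98.
- *A mixed model fitted to all starters.* This contradicts the completer rule in the sentence before it. In the same data set it gave −0.086; the change in all 344, had everyone been observed, was −0.110.

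No reading works with the text as it stands. This step needs no assumption.

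**3. How far can completers differ from all starters?** Assume equal SDs at t0 and t1, pre-post correlation r, and dropout that depends on the t0 score only. Then:

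- Expected change given baseline = constant − (1 − r) × baseline.
- Let the gap be the dropouts' mean t0 score minus the completers' mean, in SD. With 30% dropout, the completers' baseline mean lies 0.30 × gap below that of all starters.
- Completer change − all-starter change = 0.30 × gap × (1 − r).

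The article gives neither r nor the gap; both are assumptions here.

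| Gap (SD) | r = 0.5 | r = 0.6 | r = 0.7 |
|---|---|---|---|
| 0 | 0 | 0 | 0 |
| 0.25 | 0.038 | 0.030 | 0.023 |
| 0.50 | 0.075 | 0.060 | 0.045 |
| 0.75 | 0.113 | 0.090 | 0.068 |

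For scale, d = 0.20 on the change equals 0.20 × √(2(1 − r)) baseline SD, which is 0.200 at r = 0.5 and 0.179 at r = 0.6. A gap of 0.50 SD therefore shifts the result by 0.075/0.200 = 37.5% or 0.060/0.179 = about one third of the planned effect.

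**4. Simulation** (344 starters, 30% dropout depending on t0, no true change, nominal two-sided 0.025, dropouts lower at t0):

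| Gap, absolute (SD) | Rejection, r = 0.5 | Rejection, r = 0.7 |
|---|---|---|
| 0 | 0.027 | 0.028 |
| 0.25 | 0.047 | 0.038 |
| 0.475 | 0.136 | 0.076 |
| 0.84 | 0.399 | 0.233 |

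A likelihood estimate using all starters' t0 scores stayed within 0.002 SD of the true change in every cell.

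**5. Direction.** With r = 0.6, no true change and dropouts 0.50 SD *higher* at t0, the completer test rejected in 11.7% of runs, essentially all towards an increase. With a true change of −0.179 in that setting, completers showed −0.118. If dropouts start *lower*, the sign reverses.

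**6. Limit of the remedy.** With dropout depending on the t1 score instead (r = 0.6, logistic slope 0.53, true change −0.179), completers gave about −0.239 and the all-starters likelihood estimate about −0.277, which is further from the truth.

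**The case against.** The case on the other side has four parts.

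- **Completers are a coherent target.** The t1 survey takes place on completion, so non-finishers have no t1 by design. The article labels the group, sizes the study for it, and plans to report the dropout rate and compare the groups. This stands: the t-test is valid for change among completers. The article does not, however, limit its aims to them.
- **Bias is not shown.** No passage links dropout to score. This stands for size and direction. A reader might infer that the planned test produces a false finding of benefit about 12% of the time. The article does not support that: the figure needs an assumed gap of about 0.5 SD, falls to roughly 4 to 5% at 0.25 SD, and for stigma points towards *worsening* when dropouts are those with higher stigma.
- **A mixed model is no cure-all.** This stands. It helps only when dropout depends on observed data (step 6), and it does not remove regression to the mean from self-selection into the study.
- **The study is exploratory and claims no causal effect.** That lowers the severity. But the disclaimer concerns the missing control group, and the self-selection caveat concerns recruitment. Neither covers loss after t0.

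Item-level scoring rules and further descriptive comparisons could sit in a fuller plan. The REML sentence and the joint completer definition are stated in the article and need correcting there. How many people would lack only the self-efficacy scale is unknown.

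**Conclusion.** The point holds as a should-fix. Without any assumption, the REML rule is not executable as written, a secondary scale decides who enters the primary analysis, and the dropouts' t0 SOSS-SF and LOSS-SF scores have no stated use. With assumptions (30% dropout depending on t0, gap 0.25 to 0.75 SD, r 0.5 to 0.7), the completer change departs from the all-starter change by 0.02 to 0.11 SD. The direction depends on who leaves, and the difference is zero if dropout is unrelated to baseline or the pre-post slope is 1. It would be too strong to say that the primary result *is* biased, that the completer t-test is invalid, or that the sample size is wrong.

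**What to change.** 1. Replace the REML sentence with a linear mixed model per endpoint, fitted by REML with time as fixed effect and unstructured covariance, including everyone with a t0 score. Report it beside the completer t-test, and state that the t-test describes change among completers only.
2. Define the analysis set separately for SOSS-SF, LOSS-SF and self-efficacy, and list self-efficacy at t1 under Study design so that it agrees with Secondary outcome measures.
3. Add t0 SOSS-SF, LOSS-SF and self-efficacy scores to the comparison of completers with non-completers.
4. Add a sensitivity analysis for dropout that depends on the unobserved t1 score, for example by shifting the non-completers' predicted t1 scores by a range of fixed amounts. With 30% missing, a shift of δ SD moves the all-starter mean change by 0.30 × δ; at r = 0.5 it takes 0.20/0.30 = 0.67 SD to cancel the planned effect.
5. Do not add a t1 survey of non-finishers, because that would change what t1 means.

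Cost: revised wording and somewhat more analysis in software already named, with no change to 241 or 344. The drawback is two estimates per endpoint that may differ and will need explaining.

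### One completer set covering all three scales governs every test, so as written complete primary data can be excluded because another scale, including the secondary self-efficacy scale, was not completed

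*Protocol article*

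**What the plan says.** All references are to Aim 3 of the protocol article.

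- **Outcome hierarchy.** Primary outcome measures: "Primary outcome measures will be change in suicide stigma and suicide literacy", measured by SOSS-SF and LOSS-SF. Secondary outcome measures: "A secondary outcome measure will be self-efficacy expectations of dealing with psychologically difficult situations", assessed "using an interval-scaled instrument newly developed for this study (pre- and post-completion of the online intervention").
- **Tests.** Statistical analysis: "For pre-post comparisons (SOSS-SF, LOSS-SF, and self-efficacy expectation scores), we will use the t-test for dependent samples".
- **Analysis set.** Same section: "Analyses will be conducted for participants who have completed pre and post measurement of SOSS-SF, LOSS-SF, and self-efficacy expectation". This group is given the one label *completers*, and the label is used again for the comparison with people who started but did not finish.
- **Missing data.** Same section: "In case of single missing values, the restricted maximum likelihood-method will be applied". The section does not say what counts as a single missing value.
- **Sample size.** 241 pairs for d = 0.20, power 0.80 and alpha 0.05 adjusted for two endpoints, SOSS-SF and LOSS-SF. The t0 figure of 344 follows from "Assuming a dropout rate of 30" per cent, which is not broken down by scale.
- **Content of the t1 survey.** Study design: "a post-survey will be conducted using SOSS-SF and LOSS-SF again". Self-efficacy is not named there.

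**The concern.** The analysis set joins the three scales by *and*, and nothing separates the primary tests from the secondary one. Inclusion in the SOSS-SF test therefore depends on LOSS-SF and on self-efficacy, and the LOSS-SF test depends likewise on the other two. The self-efficacy condition is the hardest to justify: a secondary instrument, whose psychometric properties are to be described in this same sample, decides who enters the primary tests.

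Two things are at stake. Primary data that were observed could be discarded for a reason unrelated to the primary endpoint. And the primary sample would be selected further, on willingness to finish a secondary questionnaire twice. The sample size calculation has no separate term for such a loss.

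This is not a detail left for a later analysis plan. The article states the rule, and the question is whether the stated rule is a good one.

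**Working it through.** **1. Reproduce the planned number.** Inputs from Sample size calculation: d = 0.20, power 0.80, alpha 0.05 adjusted for two endpoints, dependent t-test. Sidedness is not stated; two-sided is taken, so alpha = 0.05/2 = 0.025.

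Power for n pairs comes from the noncentral t distribution with n − 1 degrees of freedom and noncentrality d√n, with critical value t(0.9875; n − 1).

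- n = 240: power 0.7997
- n = 241: noncentrality 0.20 × √241 = 3.105, power 0.8015

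The smallest n reaching 0.80 is 241, which is the plan's figure. The normal approximation gives 237.6. Without the adjustment, alpha 0.05 would need 199 (two-sided) or 156 (one-sided), so the adjusted two-sided reading is the one that reproduces 241.

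**2. Reproduce the t0 number.** 241 / (1 − 0.30) = 344.3. The plan states 344; rounding up would give 345. The difference does not matter here. The calculation uses the two primary scales and one overall dropout rate, and self-efficacy does not enter it.

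**3. Set the rule against the sizing.** Let m be the share of participants with complete primary data who lack self-efficacy at t0 or t1, over and above the 30%. The documents give no value for m, so the rows below are assumptions. Pairs kept = 241 × (1 − m), rounded down. t0 sample needed to keep 241 = 241 / [0.70 × (1 − m)], rounded up.

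| m (assumed) | Pairs kept | Power | t0 sample to keep 241 |
|---|---|---|---|
| 0% | 241 | 80.2% | 345 |
| 5% | 228 | 77.7% | 363 |
| 10% | 216 | 75.2% | 383 |

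Each further 5% costs about 2.5 points of power. With m = 0, or if the 30% already includes these people, nothing is lost.

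**4. Does the missing-data sentence rescue such participants?** If a single missing value means an isolated item, a participant who skipped one item may be kept, but one who did not complete the scale is still outside the set. If it means a whole missing scale, it contradicts the completer definition beside it, and restricted maximum likelihood is not part of a dependent t-test. On neither reading is a wholly missing scale clearly covered.

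**5. Compare the sections on t1.** Study design names only SOSS-SF and LOSS-SF for the post-survey. Secondary outcome measures and Statistical analysis both require self-efficacy before and after. The analysis set depends on which is right.

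**The case against.** The sentence could be meant scale by scale: it repeats the list of pre-post comparisons, and the word *completers* is there mainly to separate people who reached t1 from those who dropped out. That reading is possible, but one label for one group, reused in the dropout comparison, points to a common set. If scale-by-scale was intended, the text should say so.

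The loss may be negligible. All three scales are planned for the same occasions, so someone who leaves before t1 loses all of them together, which is ordinary dropout. The missing-data sentence may keep people who skipped isolated items. The 30% is not defined and can be read as covering everyone outside the completer set. All of this stands, and it limits the size of the point.

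The selection effect is also modest. The sample already consists of people who finish an intervention of 1.5 to 3 hours in an uncontrolled, exploratory study that disclaims causal attribution. A common set with one N for all outcomes is a recognised, if less efficient, choice.

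Three stronger readings are tempting and are not supported:

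- *The analysed number will fall below 241.* This needs a loss rate the documents do not give, and a 30% allowance that does not already contain it.
- *Relatives and interested persons will be lost from the LOSS-SF test because the self-stigma wording does not apply to them.* Primary outcome measures also describes a perceived-stigma version, which needs no suicidality of one's own. Nothing says both versions are required. The eligibility section admits these groups, and Statistical analysis plans subgroup and regression analyses by nature of suicide experience, which would make no sense if they were removed.
- *Nobody can be a completer because self-efficacy is not measured at t1.* Two other sections plan it at both times, so an incomplete sentence in Study design is the likelier explanation.

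**Conclusion.** The point holds as a defect in a stated rule. As written, a participant with complete data on a primary scale is excluded from that scale's test for not completing another scale, including the secondary, newly developed self-efficacy instrument. The documents give no purpose that this condition serves, and it does not match a sample size built on the two primary endpoints.

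Its size is unknown. If an additional 5% or 10% of pairs were lost, power would be 77.7% or 75.2% instead of 80.2%, taking d = 0.20, two-sided alpha 0.025 and 241 pairs as the starting point. It may be nil. The case for changing the rule rests on its wording and on how little the change costs, not on a demonstrated loss of power.

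**What to change.** In Statistical analysis, replace the single completer set with a set for each endpoint, for example: *Each scale is analysed in all participants with t0 and t1 data on that scale; the number analysed is reported for each endpoint. The set with all three scales complete at both times is used as a sensitivity analysis.* Completeness of self-efficacy is then required only for the self-efficacy analysis.

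In the same edit, reconcile the Study design description of the t1 survey with Secondary outcome measures, so that it is clear whether self-efficacy is collected at t1.

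The cost is a sentence or two in the analysis section and one correction elsewhere. The N may differ slightly between endpoints and has to be shown for each. Compared with the present rule, the change cannot reduce the number analysed for either primary scale, and it leaves the sample size calculation as it is.

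### The missing-value rule names REML, which cannot operate in a completers-only paired t-test, and the t0 outcome scores of participants who stop enter no stated analysis

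*Protocol article*

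**What the plan says.** The Aim 3 Statistical analysis section of the protocol article makes these statements about the outcome scales.

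- Test, for SOSS-SF, LOSS-SF and self-efficacy: "we will use the t-test for dependent samples (all three scales are interval-scaled".
- Analysis set: "Analyses will be conducted for participants who have completed pre and post measurement of SOSS-SF, LOSS-SF, and self-efficacy expectation".
- Missing values: "In case of single missing values, the restricted maximum likelihood-method will be applied".
- Those who stop: "Participants who have started the intervention but have not completed will be compared to completers in terms of age, gender, and nature of suicide experience", where data are available. A dropout rate is also calculated.

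The Aim 3 Study design section states that before the intervention starts, "attitudes and knowledge on suicidality (SOSS-SF and LOSS-SF) are collected". The Sample size calculation is for a "dependent t-test, alpha adjusted for two endpoints: SOSS-SF and LOSS-SF", and continues: "Assuming a dropout rate of 30%, a sample of *N* = 344 is needed at the beginning of the intervention".

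The article names no mixed model or other likelihood model, and gives no rule for scoring a scale with an unanswered item.

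**The concern.** The article fixes a test, an analysis set and a missing-value method in adjoining sentences, and the third does not fit the first two. Whoever analyses the data must set one of them aside, possibly after seeing the data, and this affects both primary outcomes. Until that is settled, a participant with one unanswered item may be dropped, or may be scored by a rule chosen late.

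The second issue is what happens to people who stop. SOSS-SF and LOSS-SF are measured before the intervention starts, so these scores can exist for everyone who begins. The completer rule leaves them unused for those who stop, and the planned dropout comparison does not include them. The reader will therefore not learn whether people who stopped began with more stigma or less knowledge. The Discussion makes keeping the intervention online conditional on its meeting its aims, so the estimate has practical consequences.

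**Working it through.** **1. The plan's own figures.** Inputs from Sample size calculation: d = 0.20, power 0.80, alpha 0.05 adjusted for two endpoints, 30% dropout. Two-sided testing is not stated; it is inferred because it reproduces the result. Exact paired t-test power (noncentral t) at alpha 0.05/2 = 0.025 gives n = 241 (power 0.8015). Then 241/(1 - 0.30) = 344.3, stated as 344. The figures are sound. They confirm that 344 - 241 = 103 starters are expected to fall outside the outcome analysis.

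**2. Can the REML rule operate?** There are three readings of a single missing value.

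- *A missing scale score.* That person lacks a pre or post measurement and is outside the completer set. On complete pairs REML adds nothing: in one simulated data set of 241 pairs, a REML random-intercept model and the paired t-test gave the same difference (-0.201) and the same t (-3.488).
- *A missing item within a scale.* A REML model fitted to scale scores returns no item value and no scoring rule.
- *A mixed model on everyone with t0 data.* This is coherent, but it is not named, and it conflicts with both the t-test and the completer restriction.

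**3. Change in completers against change in all starters (assumed values).** Let SD = 1 at both times, r the pre-post correlation, and g the t0 mean of those who stop minus that of completers. With 30% stopping, completers lie 0.30 × g below the mean of all starters at t0. If stopping depends only on t0 and the regression of t1 on t0 is linear:

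completer change = -0.20 + (1 - r) × 0.30 × g

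| r | g | Completer change |
|---|---|---|
| 0.5 | 0.30 | -0.20 + 0.5 × 0.090 = -0.155 |
| 0.7 | 0.30 | -0.20 + 0.3 × 0.090 = -0.173 |
| 0.5 | 0.56 | -0.20 + 0.5 × 0.168 = -0.116 |
| 0.7 | 0.56 | -0.20 + 0.3 × 0.168 = -0.150 |

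Simulation with logistic dropout on t0 agrees: -0.156 and -0.173 at a gap near 0.29, and -0.118 and -0.151 at a gap near 0.55. Likelihood estimation that keeps all t0 scores returns -0.20. With g = 0 both give -0.20. A negative g would push the completer estimate beyond -0.20. The article gives neither g nor r.

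**4. Precision when stopping is unrelated to t0.** Variance of mean change:

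- completers: 2(1 - r)/241
- mixed model: (1 - r²)/241 + (1 - r)²/344

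For r = 0.5: 0.003839/0.004149 = 0.925. For r = 0.7: 0.002378/0.002490 = 0.955. The gain is 4 to 8% of variance.

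**5. Item loss if no workable rule exists (assumed independent skip rates).** One 16-item SOSS-SF version at two time points is 32 items. At 0.2% skipped per item, 0.998^32 = 0.938, leaving 226 of 241 pairs (power 77%). At 0.5%, 0.995^32 = 0.852, leaving 205 pairs (power 73%).

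**The case against.** The strongest reply has four parts.

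*The wording allows a conditional reading.* People who completed both surveys might still lack a single score, and for those cases a REML-estimated model would replace the t-test. The article is also condensed. This softens the contradiction but does not remove it. That reading still needs a mixed model the text never names, and it still gives no value for a missing item. The article states a method that does not work; it does not merely defer one.

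*Completers are the declared target.* t1 is defined as completion of the intervention, the study is described as exploratory, and causal attribution is disclaimed. This stands. A reader might infer that the completer t-test is simply biased. The documents do not support that: for change among completers, dropout that depends on t0 causes no bias. The discrepancy arises only when the result is read as change in all starters.

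*The data of those who stop are used.* Age, gender and suicide experience enter the dropout comparison, so it would be wrong to say that all their t0 data are discarded. Only the t0 outcome scores go unused.

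*The magnitudes are assumed.* This also stands. The simulated dropout depends on t0 alone, which is the condition under which the mixed model recovers -0.20. Skip rates have no source, and the article does not say whether online items can be skipped. A larger item loss follows if everyone answers both adapted SOSS-SF versions (64 items: 212 or 174 pairs, power 74% or 65%). However, the self-stigma version concerns one's own suicidality, while close persons and other interested people may also take part.

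**Conclusion.** The point holds in two parts. First, the REML rule cannot operate alongside the paired t-test and the completer set. This follows from the text and depends on no assumed number. Second, the t0 SOSS-SF and LOSS-SF scores of about 103 of 344 expected starters enter no stated analysis, so the plan can neither show nor adjust for stopping that depends on them. The effect on the estimate cannot be computed from the article. In the illustration, a true change of -0.20 SD in all starters appears as -0.12 to -0.17 in completers; with no dependence there is no difference, and the mixed model's gain is then only 4 to 8% of variance. The sample size itself is correct. This should be corrected before analysis, but it does not invalidate a completer result that is reported as such.

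**What to change.** - For each scale, estimate pre-post change in all participants with a t0 score by a linear mixed model (fixed effect of time, unstructured 2×2 covariance, REML, SPSS MIXED). Keep the dependent t-test in completers as a sensitivity analysis.
- Add t0 SOSS-SF and LOSS-SF to the comparison of completers with non-completers.
- Remove REML as the rule for missing items. Pre-specify a scoring rule for each scale: within subscale for SOSS-SF, whose three factors should not fill in for one another, and separately for the true/false LOSS-SF items. One person-mean rule across all scales would not suit them.

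The cost is analysis wording only. It needs no extra participants or measurements, and SPSS 25 is already planned. The downside is that the mixed model relies on missingness at random given t0 and estimates the change expected had all starters completed. The completer result should therefore be reported beside it.

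### The sample size splits alpha over the two primary endpoints, but the analysis section tests everything at 0.05, so the planned error control is not carried into the decision rule

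*Protocol article*

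**What the plan says.** Three sections of the protocol article under Aim 3 bear on this.

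- **Sample size calculation.** The plan gives 241 for a pre-post comparison, which "will be necessary to identify an effect size of d = 0.20", "with a power of 0.80 and a significance level of α = 0.05". In brackets it adds the basis: "dependent t-test, alpha adjusted for two endpoints: SOSS-SF and LOSS-SF". The adjusted level is not printed, and neither is the sidedness. With 30% dropout the number at t0 is 344.
- **Primary outcome measures.** "Primary outcome measures will be change in suicide stigma and suicide literacy", measured by SOSS-SF and LOSS-SF. These are the two endpoints named in the sample size calculation.
- **Statistical analysis.** Paired t-tests are planned for SOSS-SF, LOSS-SF and the self-efficacy score, followed by subgroup and regression analyses. The section closes with: "For all analyses α ≤ 0.05 will be considered statistically significant". It mentions no adjusted level, testing order or separate rule for the primary scales.

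**The concern.** The sample size calculation commits to a multiplicity adjustment over two primary endpoints. The section that says how results will be judged sets one threshold for everything, and that threshold is the unadjusted one. An analyst who follows the analysis section would call p = 0.04 on either primary scale significant. An analyst who follows the sample size section would not, under an equal split.

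Adjusting for two endpoints makes sense only if either one alone can support a claim, and that is the situation in which testing each at 0.05 inflates the error rate. The result also has a practical use: according to the Discussion, whether the intervention stays on the portal depends on its having met its aims. What counts as meeting them should not depend on which section is read.

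**Working it through.** **Inputs.** From the Sample size calculation section: dependent t-test, d = 0.20, power 0.80, nominal alpha 0.05, adjustment for two endpoints, 241 completers, 30% dropout, 344 at t0. From the Statistical analysis section: threshold 0.05 for every analysis. Assumed, because not given: two-sided tests, and the correlation between the two test statistics.

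**Step 1: reproduce the plan's figure.** For a paired t-test with d as mean change over the SD of change, power comes from the noncentral t distribution with n − 1 degrees of freedom and noncentrality d√n. The smallest n reaching 0.80 at d = 0.20 is:

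| Level per endpoint | Exact paired t | Normal approximation |
|---|---|---|
| 0.025 two-sided (0.05/2) | **241** | 238 |
| 0.0253 two-sided (Šidák) | 240 | 237 |
| 0.05 two-sided (no adjustment) | 199 | 197 |

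The normal approximation is n = ((z for alpha + z for power)/d)²:

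- at 0.025, ((2.241 + 0.842)/0.20)² ≈ 237.6, rounded up to 238;
- at 0.05, ((1.960 + 0.842)/0.20)² ≈ 196.2, rounded up to 197.

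The stated 241 is the exact result at two-sided 0.025. A one-sided test at 0.0125 gives the same 241. The unadjusted level does not give it, so the adjustment was used in the calculation. It accounts for 241 − 199 = 42 pairs.

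Dropout: 241/0.70 = 344.3, stated as 344. Strict rounding up would give 345; the difference is immaterial.

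**Step 2: power at 241 pairs.** At two-sided 0.025 it is 80.2% per endpoint. At two-sided 0.05 it is 87.1%.

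**Step 3: chance of at least one false-positive primary result.** For two independent tests this is 1 − (1 − α)²:

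- at 0.05 each: 1 − 0.95² = 0.0975;
- at 0.025 each: 1 − 0.975² = 0.0494.

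For correlated tests, the same probability from a bivariate normal distribution with an assumed correlation is:

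| Assumed correlation | 0.05 each (analysis section) | 0.025 each (sample size basis) |
|---|---|---|
| 0 | 9.8% | 4.9% |
| 0.3 | 9.5% | 4.8% |
| 0.5 | 9.1% | 4.6% |
| 0.8 | 7.8% | 4.0% |

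The split used for sizing keeps the rate at or below 5% throughout. The threshold in the analysis section does not.

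**Step 4: a conditional extension.** On the SOSS-SF, the primary outcome section says "we will adapt the SOSS-SF from a general measure of suicide stigma to assess (1) negative attitudes towards oneself", and separately to assess perceived stigma. If these became two separate primary tests, there would be three tests with literacy. At 0.025 each and independent, the error would be 1 − 0.975³ = 0.073. An equal three-way split (0.0167 two-sided) would need 265 pairs for 80% power; at 241 pairs the power would be 75.6%.

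**The case against.** **0.05 may be meant as the overall level.** The sample size section itself quotes 0.05 and gives the adjustment separately in brackets. The analysis section also writes α, whereas the telephone survey section writes p. On that reading 0.05 is the family-wise level, and the split over two endpoints still applies underneath it. The reading is possible, but the sentence does not fit it. The sentence covers primary, secondary, subgroup and regression tests alike, and no single family-wise level is being shared across all of those. It works as a per-test threshold, as the parallel sentence does for the survey.

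**The detail may be left to a fuller document.** How an adjustment is carried out often is. But the article is not silent here: it states a threshold, and that threshold conflicts with its own sample size basis.

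**The study is exploratory.** This stands, and it limits the severity. The design sections decline randomisation on exploratory grounds, and the limitations say that changes cannot be attributed causally to the intervention. In an uncontrolled comparison of completers, the choice between 0.025 and 0.05 is not the main threat to interpretation. It does not remove the inconsistency, because the protocol itself named primary endpoints, chose to adjust for them and sized the study accordingly.

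**Stronger readings that a reader might infer, and that the documents do not support:**

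- *That the error rate is 14.3%*, from three independent tests at 0.05 (1 − 0.95³). The sample size section counts two endpoints, and nothing says that self-stigma and perceived stigma will be separate primary tests. Independence would also be doubtful for two adaptations of one instrument.
- *That 241 proves a two-sided 0.025 test.* The level and sidedness are not printed, and one-sided 0.0125 gives the same number.
- *That the sample size is wrong.* It is consistent with the stated adjustment; the fault lies in the analysis threshold.

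**Conclusion.** The point holds. The sample size section adjusts alpha for SOSS-SF and LOSS-SF, and the analysis section sets an unadjusted 0.05 that covers those same two tests. Followed as written, the analysis rule gives a 7.8% to 9.8% chance of at least one false-positive primary result, against an intended 5% or less.

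That range assumes two-sided tests, two primary tests, success on either one being enough for a claim, and a correlation between 0.8 and 0. None of these is stated outright, although an adjustment for two endpoints implies the second and third.

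Severity is moderate. Sample size, estimates and design are unaffected. Only primary results with p between 0.025 and 0.05 would be judged differently, in a study that describes itself as exploratory and makes no causal claim.

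**What to change.** Amend the closing sentence of the Aim 3 Statistical analysis section to say that:

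- SOSS-SF and LOSS-SF are each tested two-sided at 0.025, or by the Holm procedure at an overall two-sided 0.05;
- all other tests (self-efficacy, subgroup, regression and completer comparisons) use 0.05 and are exploratory.

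Print the adjusted level and the sidedness in the Sample size calculation section as well, so that the two sections can be seen to agree. If confidence intervals are to match the decisions, 97.5% intervals go with the fixed 0.025 split; they do not correspond to Holm decisions.

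State whether the SOSS-SF contributes one primary test or two. If self-stigma and perceived stigma are to be tested separately, apply Holm across all three primary tests, since 0.025 each would leave up to about 7.3% if they are independent.

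For two primary tests the cost is a sentence or two. The sample size stays at 241 completers and 344 at t0. Power per endpoint is the planned 80.2%, not the 87.1% that the looser threshold would give. The change should be made before any outcome data are analysed, because a threshold chosen after seeing p-values between 0.025 and 0.05 would not be credible.
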